## Abstract

**Background:**

In women, anorectal infections with *Chlamydia trachomatis* (CT) are about as common as genital CT, yet the anorectal site remains largely untested in routine care. Anorectal CT frequently co-occurs with genital CT and may thus often be treated co-incidentally. Nevertheless, post-treatment detection of CT at both anatomic sites has been demonstrated. It is unknown whether anorectal CT may play a role in post-treatment transmission. This study, called FemCure, in women who receive routine treatment (either azithromycin or doxycycline) aims to understand the post-treatment transmission of anorectal CT infections, i.e., from their male sexual partner(s) and from and to the genital region of the same woman. The secondary objective is to evaluate other reasons for CT detection by nucleic acid amplification techniques (NAAT) such as treatment failure, in order to inform guidelines to optimize CT control.

**Methods:**

A multicentre prospective cohort study (FemCure) is set up in which genital and/or anorectal CT positive women (*n* = 400) will be recruited at three large Dutch STI clinics located in South Limburg, Amsterdam and Rotterdam. The women self-collect anorectal and vaginal swabs before treatment, and at the end of weeks 1, 2, 4, 6, 8, 10, and 12. Samples are tested for presence of CT-DNA (by NAAT), load (by quantitative polymerase chain reaction -PCR), viability (by culture and viability PCR) and CT type (by multilocus sequence typing). Sexual exposure is assessed by online self-administered questionnaires and by testing samples for Y chromosomal DNA. Using logistic regression models, the impact of two key factors (i.e., sexual exposure and alternate anatomic site of infection) on detection of anorectal and genital CT will be assessed.

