### Defining alternate anatomic site exposure

The process of CT anorectal acquisition from her own genital CT infection and vice versa is defined based on the CT test results. Exposure is defined as presence of CT detection at the other anatomic site at the same sampling moment and/or the previous sampling moment. CT typing results are also used to confirm the link between the two detections.

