### Statistical analyses

The main study questions will be answered by analysing the data on the level of episodes. For each incident CT detection, the information of the preceding sample results, and the sexual behaviour information from the preceding 2-week interval, is analysed. Using mixed models, univariate and multivariate logistic regression analyses will be applied to calculate rates of incident CT anorectal and genital detection, controlling for repeated measurements in a person. Thereby, the relative contributions are assessed of sexual exposure and of alternate anatomic site exposure, i.e., sexual transmission and self-infection. This will be done by including different exposures as co-factors and this will also be done comparing categories of sexual exposure, anatomic site exposure, and both exposures compared to no such exposure (see Table 2).

**Table 2 Tab2:** Main regression models in FemCure study

	Exposure categories	Definition in the data^b^	Interpretation^c^ of positive CT test result
Outcome incident genital CT detection			
Model 1	Sexual exposure^a^	Genital sexual exposure (at T_x_)	
	Alternate site exposure	Anorectal CT positive (at T_x_ and/or T_x-2_)	
Model 2	No exposure	No genital sexual exposure (at T_x_) AND anorectal CT negative (at T_x_ and T_x-2_)	Persistence
	Genital sexual exposure only	Genital sexual exposure (at T_x_) AND anorectal CT negative (at T_x_ and T_x-2_)	Sexual transmission
	Anorectal site exposure only	No genital sexual exposure (at T_x_) AND anorectal CT positive (at T_x_ and/or T_x-2_)	Transmission from anorectal site
	Sexual exposure and anorectal site exposure	Genital sexual exposure (at T_x_) AND anorectal CT positive (at T_x_ and/or T_x-2_)	Sexual transmission AND/OR Transmission from anorectal site
Outcome incident anorectal CT detection			
Model 1	Sexual exposure^a^	Anorectal sexual exposure (at T_x_)	
	Alternate site exposure	Genital CT positive (at T_x_ and/or T_x-2_)	
Model 2	No exposure	No anorectal sexual exposure (at T_x_) AND genital CT negative (at T_x_ and T_x-2_)	Persistence
	Anorectal sexual exposure only	Anorectal sexual exposure (at T_x_) AND genital CT negative (at T_x_ and T_x-2_)	Sexual transmission
	Genital site exposure only	No anorectal sexual exposure (at T_x_) AND genital CT positive (at T_x_ and/or T_x-2_)	Transmission from genital site

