	Sexual exposure and genital site exposure	Anorectal sexual exposure (at T_x_) AND genital CT positive (at T_x_ and/or T_x-2_)	Sexual transmission AND/OR Transmission from genital site

^a^Based on self-administered questionnaires and semen biomarker assessment

^b^T_x:_ test result at the sampling; T_x-2:_ test result at the sampling two weeks earlier

^c^Strain typing is used to further aid interpretation of the observed positive CT test result, specifically to confirm self-infection (i.e., strain types do not differ between anatomic sites) or persistence (i.e., strain types do not differ over time)

Risks will be expressed by odds ratio‘s and 95 % confidence intervals. Co-factors (such as age, but also treatment-type) will be included in the models to account for their potential role as a confounding factor or effect-modifier in the associations between exposure and CT detection. Also, these co-factors are assessed for their association with CT detection.

Sensitivity analyses will be undertaken by varying the definition of the outcome (primary and secondary outcomes) and by varying the definition of the sexual exposure (e.g., including and excluding sexual practices). By performing a (limited) process evaluation of our study, we will obtain insights in the factors that have affected participation and possible loss-to-follow-up.

In a sub analysis, in which the unit of analysis will be an individual woman (not the 2-week episodes), a head-to-head comparison of the two treatments will be conducted.

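### Table 2 drops sex before a still-negative previous swab, so some sexually acquired infections are read as persistence or self-infection

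*Protocol article*

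**What the plan says.** The abstract only names the two factors: the models will assess "the impact of two key factors (i.e., sexual exposure and alternate anatomic site of infection) on detection of anorectal and genital CT". The definitions are in the Methods of the protocol article.

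- **Sexual exposure.** Under *Statistical analyses*, for each incident detection "the sexual behaviour information from the preceding 2-week interval, is analysed". Table 2 accordingly enters sex at T_x only.
- **Other-site exposure.** Under *Defining alternate anatomic site exposure*: "Exposure is defined as presence of CT detection at the other anatomic site at the same sampling moment and/or the previous sampling moment". Table 2 repeats this as "Anorectal CT positive (at T_x_ and/or T_x-2", and a footnote defines T_x-2 as the "test result at the sampling two weeks earlier".
- **Model 2 categories (genital outcome).** The reference is "No genital sexual exposure (at T_x_) AND anorectal CT negative (at T_x_ and T_x-2", and a detection there is interpreted as persistence. The category "No genital sexual exposure (at T_x_) AND anorectal CT positive (at T_x_ and/or T_x-2" is interpreted as transmission from the anorectal site. The anorectal outcome mirrors this.
- **Persistence elsewhere.** *Definition of transmission* links possible persistence to a detection that follows another detection. It puts no two-week limit on the sex that counts for sexual transmission.
- **Sensitivity analyses.** The plan mentions "varying the definition of the sexual exposure (e.g., including and excluding sexual practices". No change of look-back is named.

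**The concern.** A newly acquired infection may need some days before a swab turns positive. A site that is positive at T_x-2 was probably a possible source before that sampling too, so an infection from it that was still undetectable at T_x-2 is credited to it at T_x. Sex shortly before T_x-2 gets no such credit.

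If the woman reports no sex between T_x-2 and T_x, a sexual acquisition from the earlier interval enters one of the two no-sex categories and takes the label attached to it. The relative contribution of sexual transmission and self-infection is the main analysis and feeds the practical recommendations. The error runs in one direction: it adds sexual acquisitions to the categories that are meant to contain none.

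**Working it through.** **1. Tracing one case through Table 2.** Sex before T_x-2; swab negative at T_x-2; swab positive at T_x; no sex in the last interval.

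| Other site at T_x and T_x-2 | Model 2 category | Reading in Table 2 |
|---|---|---|
| Negative at both | No exposure | Persistence |
| Positive at either | Other-site exposure only | Transmission from the other site |

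The first reading also sits badly with *Definition of transmission*, because this detection follows a negative sample. If the woman did have sex in the last interval, the case lands in a sexual-exposure category and nothing is lost.

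**2. Inputs.** From *Numbers and power*: sex in p = 20-60% of two-week episodes. Assumed, because the article gives no values: delay from acquisition to a positive swab L = 3-7 days; acquisition spread evenly over the 14 days; correlation r of sex between adjacent episodes, 0 or 0.5; background risk b = 2% per episode; sexual acquisition a = 4 percentage points. The stated sample size plays no part in this point.

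**3. Share of sexual acquisitions first detected in an episode scored as without sex.** Share = (L/14) x (1 - p) x (1 - r).

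| p | L = 3, r = 0 | L = 7, r = 0 | L = 3, r = 0.5 | L = 7, r = 0.5 |
|---|---|---|---|---|
| 20% | 17.1% | 40% | 8.6% | 20% |
| 40% | 12.9% | 30% | 6.4% | 15% |
| 60% | 8.6% | 20% | 4.3% | 10% |

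If 80% of women with sex in one interval also have it in the next, the share is (L/14) x 0.2, which is 4.3% at 3 days and 10% at 7 days.

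**4. Effect on the odds ratio at p = 40%.** Let f = L/14. Risk with sex at T_x is b + a(1 - f) + a f P(earlier sex | sex now). Risk without is b + a f P(earlier sex | no sex now). These two probabilities are 0.4 and 0.4 at r = 0, and 0.7 and 0.2 at r = 0.5. With no delay the odds ratio is (0.06/0.94)/(0.02/0.98) = 3.13.

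| | Risk, sex at T_x | Risk, no sex at T_x | Odds ratio | Share of no-sex detections that are sexual |
|---|---|---|---|---|
| r = 0, L = 3 | 5.49% | 2.34% | 2.42 | 0.34/2.34 = 15% |
| r = 0, L = 7 | 4.80% | 2.80% | 1.75 | 0.80/2.80 = 29% |
| r = 0.5, L = 3 | 5.74% | 2.17% | 2.74 | 0.17/2.17 = 8% |
| r = 0.5, L = 7 | 5.40% | 2.40% | 2.32 | 0.40/2.40 = 17% |

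**5. Would pooling both intervals into one exposed category be better?** At r = 0 the pooled group is 64% of episodes, with risk (0.16 x 6% + 0.24 x 8%)/0.64 = 4.5%. (The 8% is the sum of the risks in the two cells with sex in one interval only.) The odds ratio is 2.31 whatever the delay. At r = 0.5 the risk is (0.28 x 6% + 0.12 x 8%)/0.52 = 5.08%, odds ratio 2.62. Against step 4, pooling is worse at 3 days (2.31 against 2.42; 2.62 against 2.74) and better at 7 days (2.31 against 1.75; 2.62 against 2.32). At p = 20%, r = 0 and 3 days it is clearly worse (2.16 against 2.53).

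**6. Keeping the intervals apart.** Against no sex in either interval (risk 2%), sex in the earlier interval only has risk 2% + 4% x f. That is 2.86% at 3 days (odds ratio 1.44) and 4% at 7 days (odds ratio 2.04). Sex in both intervals has risk 6% and returns 3.13 at either delay.

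**The case against.** **The windows nominally coincide.** T_x-2 is the start of the same two-week interval over which sex is counted. A reader might infer that the other site is simply given twice the look-back of sex. The documents do not support that: one factor is a point measurement at both ends of the interval, the other a report across it. What remains is narrower. A positive swab at T_x-2 stands for exposure before that date, while sex before that date is dropped.

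**The size is assumed.** This stands. The article gives no detection delay, base risk or correlation, and independence between fortnights is doubtful for women with ongoing partners.

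**A wider definition is not clearly better.** This stands too. Step 5 shows that pooling brings in sex that did not cause the detection, and can dilute the odds ratio.

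**Other parts of the plan may catch it.** The sensitivity analyses are given by example, and an unseen full analysis plan may include a lag. Strain typing is meant to confirm persistence and self-infection. But the only example offered concerns practices, not timing. Typing is done in a subset, aids interpretation without changing the model categories, and cannot separate persistence from reinfection by the same partner with the same strain. *Limitations* concedes misclassification of exposure and outcome, but for outcomes mentions only clearance before sampling.

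**An incident positive can still be persistence.** A treated infection may go undetected once and reappear. That makes the persistence reading possible; it does not make it the default.

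**Conclusion.** The point holds in limited form. As defined, Table 2 places some sexually acquired infections in its no-sex categories, labels them persistence or self-infection, and lowers the apparent contribution of sex. It affects only women without reported sex in the last interval. At 40% sex and an assumed delay of 3-7 days, that is about 13-30% of sexual acquisitions under independence and 6-15% at correlation 0.5. In the illustrative model the odds ratio falls from 3.13 to between 1.75 and 2.74. The direction follows from the definitions; every size rests on the assumptions listed.

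Two stronger readings go too far. One is that the T_x definition is wrong and must be replaced: under short delays the pooled alternative performs worse. The other is that the odds ratio for self-infection is inflated. More detections receive that label, but the reference group is contaminated as well, so the direction for that odds ratio is not established.

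**What to change.** 1. Keep sex at T_x as the primary definition.
2. In Model 1, add post-treatment sexual exposure reported at the previous sampling as a separate lagged term. Report both terms, because neither alone carries the whole effect of sex.
3. Prespecify a Model 2 sensitivity analysis in which sex in the earlier interval only is its own category, or in which the reference requires no sex in both intervals. Do not pool the two intervals as a replacement for the primary definition.
4. Do not interpret *No exposure* detections as persistence on the two-week window alone. Align that label with *Definition of transmission* and with strain typing where available.

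No new data are needed: Table 1 has a questionnaire at every sampling, and *Collection of self-reported data* gives a two-week recall. For the week 2 sample the earlier interval lies before treatment, so the lagged term is informative from week 4 on.

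The cost is precision. A reference free of sex in both intervals holds 0.6 x 0.6 = 36% of episodes instead of 60% (40% sex, independence), with wider confidence intervals.

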**Discussion:**

The FemCure study will provide insight in the role of anorectal chlamydia infection in maintaining the CT burden in the context of treatment, and it will provide practical recommendations to reduce avoidable transmission. Implications will improve care strategies that take account of anorectal CT.

**Trial registration:**

ClinicalTrials.gov Identifier: NCT02694497.

## Background

*Chlamydia trachomatis* (CT) infection is the most commonly reported sexually transmitted infection (STI) in high income countries; about 3-4 % of 18–24 year olds in the general population of European Union Member States are infected with CT [1–3]. Most infections occur in the young and the burden of sequelae is largest in women [4–6]. CT is a major cause of pelvic inflammatory disease, ectopic pregnancy and tubal infertility in women and of urethritis in men and proctitis in men who have sex with men (MSM) [4]. CT repeat infections are common in women [7], and are related to an increased risk of adverse reproductive outcomes [8]. Moreover, CT genital and anorectal infections facilitate the acquisition and transmission of HIV infection [4, 9]. Much of the burden of bacterial STI results from their frequent initial asymptomatic nature, and many infections remain undiagnosed [4]. Chlamydia is widely recognized as a public health problem and many countries have adopted control strategies to limit its spread. Measures include active testing in young people, additional population screening programs and enhanced screening activities at general practitioners [10–12]. Yet, it is clear that we fail to sufficiently limit the ongoing transmission as CT prevalence and incidence rates remain high.

Two knowledge gaps can be identified in the evidence for CT control strategies. First, we do not understand the role of anorectal CT in women in overall CT spread. In women, anorectal infections are about as common as genital infections, with proportions positive ranging between 7 - 27 % of anorectally tested women [13-25]. Yet, most anorectal CT infections remain undetected as general practitioners, hospital and population testing initiatives ignore anorectal CT and largely focus on genital CT [26]. STI clinics do test women at the anorectal site on indication, i.e., when they report anal sex or symptoms. Still, with half of all anorectal CT occurring in women who do not report anal sex, many anorectal infections are left untested. Second, we do not know whether transmission of CT can occur in the weeks following currently recommended treatment. Prior studies have shown considerable detection of both anorectal and genital CT after treatment in women and men [27–32]. Detection rates depended on the number of samples taken and type of tests used, demonstrating up to 40 % of treated cases having at least one positive sample when sampled multiple times within 8 weeks [27]. Indeed, repeat genital CT infections are common following treatment, varying between 10 % and 30 % when re-testing CT positive treated women between 3 months and a year later [33]. Guidelines advise such re-screening at 3 months after a CT diagnosis. Yet, in practice, re-screening occurs in less than a third of patients in the Netherlands [34]. Current care does not include a routine re-test of patients within 3 months of treatment [35-37] nor does it include an anorectal re-test 3 months after the genital CT treatment. Many uncertainties exist on the clinical relevance of a post-treatment CT detection. It is unknown whether it reflects transmission after sexual exposure or self-infection. It is also unknown whether detection of CT nucleic acids indicates viable or nonviable CT and what organism loads are present [38]. Suboptimal treatment may possibly play a role, but evidence is inconclusive leading to considerable debate on this issue [39–42].

The current lack of anorectal testing of patients attending STI care may not pose much of a problem when the anorectal infections are effectively treated together with the genital CT infections, as 75-95 % of anorectal CT co-occur with genital CT [13]. Yet, it is unknown whether treatment efficacy is sufficient. Moreover, the lack of understanding what observed CT positivity after treatment means in terms of transmission and morbidity, may preclude any conclusions on the potential positive effect of co-incidental anorectal CT treatment. Our understanding of how anorectal CT detection may explain CT transmission is incomplete [27]. (Un-and under) treated anorectal infections may contribute to ongoing transmission of genital and anorectal CT in the population at risk, both between partners and between anatomic sites within an individual. The FemCure study is set up to contribute to filling these knowledge gaps and contribute to the evidence for effective CT control strategies.

## Methods/design

### Study aim

The aim of the FemCure study is to understand the transmission of anorectal CT infections in women who receive routine care, specifically from their male sexual partners and to and from the anal and genital region within the same woman, and also includes an evaluation of treatment-type impact.

During a period of 4 years (2016–2019) the following study questions will be addressed:What is the detection rate of anorectal and genital CT in heterosexual women in the 12 weeks after receiving standard of care for a genital/anorectal CT infection?What is the risk of incident CT detection after sexual exposure (i.e., transmission from a male partner)?What is the risk of incident CT detection in alternate anatomic sites in women (i.e., transmission from one to another anatomic site in the same woman/self-infection)?2)What are the co-factors?3)Is treatment-type associated with risk of repeat genital/anorectal CT detection?4)Which practical recommendations can be formulated for professionals involved in CT control (STI clinic workers, general practitioners, gynaecologists, medical microbiologists).

### Design

To reach the study aim, a multicentre prospective cohort study is set up among women visiting Dutch STI clinics.

### Setting

Women will be recruited from STI clinics of the Public Health Services (GGD) in Rotterdam, Amsterdam and South Limburg. According to our national registry these three participating clinics tested 31200 women for CT in 2014. Of these, 3718 (12 %) women tested CT positive [5]. Part of these women was also tested anorectally demonstrating about 600 anorectal CT infections. Among all CT positives, the majority was young (i.e., 71 % were under 25 years of age, 20 % were between 25 and 29 years of age). A substantial part of the women who tested CT positive had a low socio-economic status (SES), based on the SES score of their neighbourhood of residence (www.scp.nl), i.e., 21 % had low SES and 13 % had very low SES. Of the positive women, the majority was Dutch (61 %). Of the remainder of the positive women, 10 % were Surinamese, 4 % were Antillean, 3 % were Moroccan, and 1 % were Turkish. The majority of the non-Dutch ethnic groups were second generation migrants.

### Study population

The eligible study population is likely to reflect the current STI clinic populations. Eligible are heterosexual women with symptomatic or asymptomatic genital and/or anorectal CT infection, who are not pregnant and 18 years or older. Exclusion criteria are recent reported use of antibiotics, HIV positivity, syphilis and infection with *Neisseria gonorrhoea*. As single anorectal CT is uncommon and around 75-95 % of genital CT positive women also have anorectal CT [13–25], it is expected that of the included women only few will have anorectal CT only. The majority (75 %) expectedly will have anorectal CT in combination with genital CT, and most of the remainder will have genital CT only at inclusion in the study. Treatment occurs according to regular care and international guidelines [35–37]. Women who are anorectally tested in routine care and found anorectal CT positive are treated with a 7-day course of doxycycline 100 mg twice daily with the first dosis being directly observed. All other women receive a directly observed single dose of azithromycin 1000 mg [35–37]; these women tested genitally CT positive in routine care and were either anorectally untested in routine care or were tested anorectally CT negative.

### Recruitment

Participants will be recruited upon return for treatment at three STI clinics. Recruitment of women is expected to take approximately 1 year. At recruitment, the women receive information on the study and are referred to the study website: www.femcure.nl.

